## Methods

### Participants and procedure

The participants are a sample of 450 students aged 10–12 from primary schools in Southwest Finland. 150 children are refugees, 150 non-refugee immigrants, and 150 native-born Finnish schoolchildren. Schools are selected on the basis that they have a preparatory class where all asylum seekers and most non-refugee immigrants study for their first year after arriving in Finland. We will select one preparatory class and one regular class in each school to draft the sample for the study. The study has two time points: baseline measurements at the beginning of the school year (T_1_) and follow-up measurements at the end of the school year (T_2_). The study uses a screening battery tool to administer a variety of questionnaires and tests which are then used to give feedback about the students to teachers and multiprofessional student welfare bodies. We aim to collect all the data within one school year (2024–2025), but if the number of participants does not reach 150 in each group, a second round of data collection will take place in 2025–2026. We will conduct a small-scale pilot study in one preparatory and one regular class in Spring 2024.

### Screening battery

The screening battery (SB) gathers many kinds of data about the participants using demographic survey questions, tasks, and questionnaires. The children answer questions and complete tasks, and data is also collected from parents and teachers. The battery contains standardized and universally applicable assessments of a) cognitive functions (general intelligence, working memory, self-regulation, and self-efficacy and decision making), b) mental health (symptoms and well-being), and c) social competence. Prior to T_1_, the research group will offer a half-day training to teachers and school psychologists participating in the study on how to use the screening battery and specifically its feedback function. During the training, initial ideas and resources on how to transform the feedback into supportive actions at schools will be discussed among participating teachers and school psychologists.

The screening battery uses the Gorilla online platform to administer questionnaires and tasks (https://gorilla.sc/). Results are then transferred via an API to a Microsoft Power BI feedback tool which compiles both anonymous general (for teachers) and personalized (for multiprofessional student welfare bodies with consent from children’s parents) feedback with data visualizations and recommendations for supportive measures for students. At the end of the school year, the SB is administered again for the same classes (T_2_). The data about any supportive actions (either using the information produced by SB or not) that children may have received during the school year is also collected. The data is collected from parents, teachers, and multiprofessional student welfare bodies. The child’s own experiences of the support received are also collected during follow-up measurements. The researchers, who are all licensed psychologists and specialists in child cognitive and social skills as well as in child mental health, will be available for consultations with the schools throughout the study year, in case the school has further questions or concerns.

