### Research question

First, we want to find out how the cognitive, social, and mental health functions of refugee children compare with (a) same aged immigrant children without refugee background and (b) native-born children in Finland. We will also examine whether worse mental health (trauma-related and depressive symptoms) is linked with poorer cognitive function and social competence across the sample. We hypothesize based on earlier (limited) literature in the field, 1) that refugee children, for whom exposure to trauma is likely more common, exhibit lower levels of cognitive functioning compared to immigrant children without refugee background and native Finnish children, and 2) that mental health problems and poorer social competence explain this link.

Second, we will examine whether reliable evaluation of cognitive, social, and mental health functions of students can inform schools about supportive actions for refugee children and whether this process is different compared with non-refugee immigrant children and/or native-born Finnish children. We will look at whether children who scored above/under critical thresholds on our Screening Battery (SB) report receive supportive actions during the school year. If they do, we look at what kinds of actions inside and outside the classroom schools conduct for refugee children, and whether the output of the SB was utilized to plan this support We will further look at whether the actions are different compared to actions with non-refugee immigrant children and/or native-born Finnish children and whether the actions are different compared to actions that do not use the information produced by the screening battery.

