We will also examine whether the supportive actions are reflected in cognitive, social, and mental health functions of refugee children within their first year in Finnish schools (after controlling for other significant life changes during the study year). We will investigate whether this effect is different compared to non-refugee immigrant children and/or native-born Finnish children and if the effect is different compared to actions not using the information produced by the screening battery. We hypothesize 3) that supportive actions informed by the findings of the screening battery have a stronger positive effect than other actions. Finally, we will examine whether improvements in mental health (trauma, depression, resilience) and social functioning during the school year are associated with better performance in cognitive tests.

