To test Hypothesis 3, screening battery effects on cognitive, social, and mental health functioning will be evaluated using repeated measures ANOVAs with 2 × 3 for {T_1_, T_2_} and {children who received SB-based support, children who received non-SB-based support, children who did not receive SB-based support} among children who scored above/under critical thresholds, and following up with *t*-tests to compare means. Differences in SB-based actions will also be evaluated qualitatively. We will further use linear regression to test whether changes in mental health (trauma- and depressive symptoms) and social functioning associate with changes in cognitive functioning from T_1_ to T_2_. In addition to analyses in the whole sample, we will also do these analyses by subgroup, separately for our three groups. Classroom atmosphere, teacher self-efficacy and awareness of culturally responsive education, family functioning, child language and development as well as children’s cultural background will be used as covariates in the regression analyses and ANOVAs. Effect sizes and confidence intervals will be reported for main effects and p-value based inference will be de-emphasized based on guidelines for New Statistics [60].

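### The whole-sample Hypothesis 3 ANOVA omits class type (preparatory v regular), so a difference in one-year change between class types can be read as an effect of SB-based support

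*Protocol article*

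**What the plan says.** - **Sampling** (Participants and procedure). Schools qualify because "they have a preparatory class where all asylum seekers and most non-refugee immigrants study for their first year after arriving in Finland". Within them, "We will select one preparatory class and one regular class in each school to draft the sample for the study". Every child therefore belongs to one class type, fixed by design.
- **How support arises and is recorded.** Under Feedback tool, the teacher's report is a classroom-level summary of averages, while individual reports go to the student welfare body on request and with parental permission. Under Teacher report, the teacher states at T2 whether SB information was used and lists actions taken in the classroom. Under Screening battery, the data to be gathered are described as "The data about any supportive actions (either using the information produced by SB or not) that children may have received during the school year".
- **Hypothesis 3** (Research question): "supportive actions informed by the findings of the screening battery have a stronger positive effect than other actions".
- **Model** (Analysis plan). A 2 × 3 repeated measures ANOVA has time as one factor and support as the other, with the levels "children who received SB-based support, children who received non-SB-based support, children who did not receive SB-based support} among children who scored above/under critical thresholds". The named covariates are classroom atmosphere, teacher self-efficacy, awareness of culturally responsive education, family functioning, child language and development, and cultural background. Class type is not named.
- **Subgroups** (Analysis plan): "In addition to analyses in the whole sample, we will also do these analyses by subgroup, separately for our three groups".

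**The concern.** Support status is an observed exposure. Some of it is decided for a whole class, since a teacher who acts on the classroom report acts for all pupils in that class, and the class is of one type. Uptake of SB-based support may therefore differ between preparatory and regular classes.

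Pupils in their first year in the country may also change at a different rate over that year from settled pupils, on tests and on symptom scales, whatever support they get. If both conditions hold, class type confounds the time-by-support contrast. The direction depends on which class type uses the SB more, so the bias cannot be presumed conservative. The test at stake is the one on which the claim of benefit from SB-informed support rests.

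**Working it through.** **The plan's own figure.** The plan gives no number for this confounding. The only related figure is the sample size, which serves here as a yardstick. For d = 0.5, two-sided alpha 0.05 (sidedness assumed) and 80% power, 63 children per group are needed before clustering. With clusters of 17 and ICC 0.07 the design effect is 1 + 16 × 0.07 = 2.12, which gives about 134. With cluster-level t degrees of freedom the result is 151 (equal clusters) to 154 (variance 10). The stated 150 per group is thus reproduced and is not in dispute.

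**Formula.** Suppose support has no true effect. Let δ be the extra mean change in preparatory over regular pupils, in SD. Let p_SB and p_other be the preparatory shares among children with SB-based and with other support. Without class type in the model,

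spurious difference = δ × (p_SB − p_other).

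If π is the preparatory share among children beyond the thresholds, and r_P and r_R are the rates of SB-based support in preparatory and regular classes,

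- p_SB = π r_P / [π r_P + (1 − π) r_R]
- p_other = π(1 − r_P) / [π(1 − r_P) + (1 − π)(1 − r_R)].

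**Inputs, all assumed.** δ = 0.2 to 0.4 SD and π = 0.6, with two patterns of uptake. For simplicity every child beyond a threshold is placed in one of the two support groups.

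| Uptake, preparatory v regular | p_SB | p_other | Difference in share | Spurious difference (SD) |
|---|---|---|---|---|
| 50% v 25% | 0.30/(0.30 + 0.10) = 0.75 | 0.30/(0.30 + 0.30) = 0.50 | +0.25 | +0.05 to +0.10 |
| 30% v 50% | 0.18/(0.18 + 0.20) = 0.47 | 0.42/(0.42 + 0.20) = 0.68 | −0.20 | −0.04 to −0.08 |
| equal rates | 0.60 | 0.60 | 0 | 0 |

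The largest of these, 0.10 SD, is one fifth of the planned d = 0.5. With a wider imbalance of 0.67 v 0.33 and δ of 0.2 to 0.5 SD, the same formula gives 0.34 × 0.2 = 0.07 to 0.34 × 0.5 = 0.17 SD.

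**What the planned adjustments do.** The same formula applies within each background group.

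- *Refugee children.* If all are in their first year, nearly all are in preparatory classes, both shares are near 1 and the bias is near 0.
- *Native-born children.* Presumably all are in regular classes, so both shares are 0 and there is no bias.
- *Non-refugee immigrants.* The text puts most, not all, of their first-year pupils in preparatory classes. The shares can differ between support groups, and the bias remains.
- *Whole sample.* Cultural background as a covariate can remove the part of the difference that lies between background groups, but not the part within the immigrant group.

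**The case against.** The strongest reply is that this is ordinary confounding in a non-randomised comparison and that the plan already covers most of it. The SB is given in both class types, so SB-based support can occur in either. Cultural background, language and development, and classroom atmosphere are covariates and may absorb part of any class-type difference. The analyses are repeated by background group, and the refugee and native-born groups are probably close to uniform in class type. The illustrated bias is small against d = 0.5 and rests on inputs that the documents do not give.

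Most of this is fair, and it limits the size of the point. It does not remove it: the whole-sample analysis stays in the plan, the immigrant group is mixed, and the covariate list is explicit and omits a design variable.

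A reader might infer two stronger claims, and the documents support neither.

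- *That preparatory-class enrolment is itself non-SB support.* No section says so. Supportive actions are described as something children may or may not receive. The Research question section asks whether flagged children "report receive supportive actions during the school year. If they do, we look at what kinds of actions inside and outside the classroom", which would be an empty question for newly arrived refugee children if enrolment already counted. The sentence on collecting support data does not define the Hypothesis 3 groups; the Analysis plan does. Exact item wording may sit in the questionnaires or the full protocol, so its absence here is no fault.
- *That the contrast simply compares class types, or that the bias reaches 0.4 SD against an unsupported group from regular classes.* Both class types can appear in every support group. A 75% preparatory group against none gives 0.75 × 0.2 to 0.4 = 0.15 to 0.30 SD, and even that needs the enrolment premise. The plan also names no purely unsupported level; its second and third levels read "children who received non-SB-based support, children who did not receive SB-based support", and their overlap is a separate matter.

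**Conclusion.** The point holds in a limited form. In the whole-sample Hypothesis 3 analysis, support is not randomised and is partly set at class level, class type is fixed by the sampling, and the stated model leaves it out. A class-type difference in one-year change can therefore appear as an effect of SB-based support, in either direction. The background covariate and subgroup analyses repair this only in part.

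Under the assumed inputs the error is about +0.05 to +0.10 SD or −0.04 to −0.08 SD, and it is zero if uptake is equal across class types or if the two class types change alike. The size is illustrative. What the text does establish is the route for the bias and the omission from the covariate list.

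**What to change.** Add class type (preparatory v regular) to the Hypothesis 3 model as a between-subject factor, together with its interaction with time. The interaction is needed because the contrast of interest is in change: a main effect of class type alone shifts a child's average level over T1 and T2 and leaves the time-by-support contrast essentially untouched. Where numbers allow, also report the contrast of SB-based with other support within each class type before pooling, and tabulate support status by class type.

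Class type is known for every child from the sampling, so no new data are needed. The cost is a small loss of degrees of freedom and some collinearity with background group. With both in the model, the class-type effect is estimated largely from the immigrant children, and its imprecision should be shown with a confidence interval.

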### Feedback tool

The feedback tool collates information on participants’ cognitive, social, and mental health functioning and compiles two reports: one for the teacher and one for school health staff. The teacher report is at a classroom level and presents results as anonymized averages. The teacher data includes a categorical graphical representation (“low”, “average”, “high”) of self-regulation, intelligence, self-efficacy, resilience, depression, trauma, loneliness, altruism, and language development levels in the classroom, with clarifying depictions of these qualities and guidance for their interpretation written by clinical psychologists working in the research project. The school health service report involves individual student data. Upon request, and with the permission of the parents, the multi-professional student welfare body is offered detailed data on the individual’s results on the screening battery. This includes a graphical summary of cognitive, social, and mental health data gathered in the study compared to subsample means (refugee, immigrant, native Finnish) for each child on each variable. The individual results can also be discussed with the child him/herself.

### Tests and measures

**Demographic variables.** At T_1_, we ask the children, as well as their parents, about the children’s age, class, gender, living arrangements, and country of birth. If the country of birth is not Finland, we ask how many years they have spent in Finland, with whom they came to Finland, immigration status, place of residence, and reason for migration. At T_2_, we ask about significant life changes after T_1_, including changes in legal status in host country, family composition, significant losses or other changes in close relations, and other significant life changes. The same kind of questionnaire was used in a previous study among refugee and native-born children in Finland [10, 33]. At T_2_, we collect a list of supportive actions the child thinks they have received during the school year.

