#### Analysis plan

**Power.** In order to form profiles across different groups of children and to assess changes in cognitive, social, and mental health functions across those children who will receive SB based supportive actions and those who do not, we performed a preliminary power analysis to determine the sample size required to detect medium-sized or larger effects on these primary outcomes. Based on typical sizes of Finnish preparatory classes, we estimated the average size of each cluster to be 17, with a variance of 10. Intraclass coefficients for these outcomes are challenging to estimate, but based on our previous cluster-randomized research among war-affected children, values of 0.01–0.1 could be reasonable. With a relatively conservative estimate of 0.07 for the ICC, and setting alpha at 0.05, to achieve 80% power to detect a medium-sized (d = 0.5) or larger effect, we would need about 150 children in each group, meaning approximately 450 children in total.

**Analyses.** Means, standard deviations, and correlations will be evaluated for all variables reported by children, parents, and teachers. To test Hypothesis 1, baseline differences between the study’s three groups will be investigated using 3-way ANOVAs and followed up with *t*-tests to compare means. To test Hypothesis 2, correlation analyses will first be used to examine whether mental health (trauma-related and depressive symptoms) is associated with poorer cognitive function and social competence. Latent profile analyses (using the TidyLPA package in R) will then be run for the entire sample under each of the three dimensions: cognitive, social, and mental health. Emerging profiles will be compared with how they line up with our three groups (refugee, immigrant, native-born Finnish).

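### Support already running at T1 is not identified, so the Hypothesis 3 contrast can mix new with ongoing support, with a bias of unknown size and sign

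*Protocol article*

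**What the plan says.** The Screening battery section of the protocol article says that data are gathered on "any supportive actions (either using the information produced by SB or not) that children may have received during the school year", from parents, teachers and student welfare bodies. The child's list is taken at T2: "we collect a list of supportive actions the child thinks they have received during the school year" (Tests and measures, demographic variables). The Parental report and Teacher report sections also place their lists at T2, each beside a question on whether SB information was used. Neither section gives a start date or a time window for the actions.

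The T1 background items named for children and parents cover demographics, family, housing and migration. None asks about support currently received. The T2 questions on life changes, by contrast, are limited to events after T1.

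Hypothesis 3 (Research question) is that "supportive actions informed by the findings of the screening battery have a stronger positive effect than other actions". The Analysis plan tests it by repeated measures ANOVA over T1 and T2, among children beyond the battery's cut-offs. Of its three groups, the first two are "children who received SB-based support, children who received non-SB-based support"; the third is children without SB-based support. The covariates are classroom atmosphere, two teacher measures, family functioning, child language and development, and cultural background.

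**The concern.** The SB produces no output until T1 has been completed, so support that it prompts must begin after T1. Non-SB support has no such limit. Remedial teaching or outside therapy carried over from an earlier year counts as received in the school year as much as something begun in November.

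The outcome is change from T1 to T2. A child whose support was running before T1 may already have part of its benefit in the T1 score. Because the analysis is confined to children beyond a cut-off at T1, a child with long-running support enters only if still beyond the cut-off despite it. Either feature could make the remaining change differ from that of a child starting support afresh, whether or not SB information added anything. The groups are not randomised, and none of the listed covariates captures this. Hypothesis 3 is the study's test of whether SB-informed support works better than other support, so its answer could partly reflect when support began.

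**Working it through.** **The plan's own figure.** The inputs come from the Analysis plan: "to achieve 80% power to detect a medium-sized (d = 0.5) or larger effect", "we estimated the average size of each cluster to be 17, with a variance of 10" and "With a relatively conservative estimate of 0.07 for the ICC". Alpha is 0.05, taken here as two-sided.

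- Unadjusted n per group = 2 × (1.960 + 0.842)² / 0.5² = 62.8, so 63.
- Design effect, equal clusters: 1 + 16 × 0.07 = 2.12, giving 63 × 2.12 = 133.6, so 134.
- Design effect, unequal clusters: 1 + ((1 + 10/17²) × 17 − 1) × 0.07 = 2.161, giving 136.2, so 137. This is just over 8 clusters of 17, so 9 whole clusters = 153.
- With t quantiles on the cluster degrees of freedom, the result is about 151 (equal) to 154 (unequal).

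The stated figure of about 150 per group is therefore reproduced. It does not depend on the present point and serves only to supply d = 0.5 as a yardstick.

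**Size of a spurious difference.** Suppose SB-based and non-SB support work equally well. Let

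- g = T1–T2 gain from support begun after T1, in SD;
- f = gain still to come after T1 from ongoing support, as a fraction of g;
- p = share of the non-SB group whose support predates T1;
- q = the same share in the SB-based group.

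Mean gain in the SB-based group = (1 − q)g + qfg. Mean gain in the non-SB group = (1 − p)g + pfg. The difference, SB minus non-SB, is (p − q)(1 − f)g.

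The documents give none of these quantities. The values below are assumptions, with g = 0.5 SD chosen to match the plan's target effect.

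| f | q | p = 0.25 | p = 0.50 | p = 0.75 |
|---|---|---|---|---|
| 0 | 0 | +0.125 | +0.25 | +0.375 |
| 0.5 | 0 | +0.06 | +0.125 | +0.19 |
| 1 | 0 | 0 | 0 | 0 |
| 1.25 | 0 | -0.03 | -0.06 | -0.09 |
| 0 | 0.25 | 0 | +0.125 | +0.25 |

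For example, p = 0.75, q = 0, f = 0 gives 0.75 × 1 × 0.5 = +0.375; p = 0.75, q = 0, f = 1.25 gives 0.75 × (−0.25) × 0.5 = -0.094. The result is proportional to g, so g = 0.3 multiplies every entry by 0.6.

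Over these ranges, in which p is never below q, the difference favours the SB only if p > q and f < 1. It is zero if p = q or f = 1, and runs against the SB if p > q and f > 1. If ongoing support were commoner in the SB-based group (p < q), the signs would flip.

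**The case against.** A reader might infer that SB-based support is always new and that the comparison is therefore biased towards the SB. The documents support neither step. Research question, Screening battery and Parental report all define SB-based support by use of SB information, not by start date. Ongoing support re-planned after the SB report would count as SB-based, and so could a child with both kinds of support. Nothing in the article says how common support before T1 is, or how its effect develops. A range showing only positive values would come from setting f and q to zero, which rules out a null or negative result in advance. This part of the objection stands.

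The amount of prior support is also limited for many participants. Asylum seekers and most other immigrants spend their first year in preparatory classes (Participants and procedure), and Research question places refugee children in their first year in Finnish schools. Long-running Finnish school support is more plausible in the regular classes. This stands too. It also means that the bias could differ between the three background groups, which the plan intends to analyse separately.

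Finally, the article is condensed, and the full questionnaires may hold start dates. That is possible, and the sponsor can check it quickly. It does not settle the matter: the article does state the group definitions and covariates for Hypothesis 3, and neither uses such information.

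**Conclusion.** The point holds as a gap in how the exposure is identified, not as a demonstrated bias in favour of the SB. As written, support is listed at T2, over the whole school year where a window is given. No T1 item on current support is named, and the Hypothesis 3 analysis does not adjust for support already running at T1. The contrast can therefore combine children starting support with children continuing it.

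Under the stated assumptions, with equally effective support and g = 0.5 SD, the spurious difference lies between about -0.09 and +0.375 SD. A tilt towards the SB is plausible if ongoing support has largely levelled off and is commoner in the non-SB group, but the documents establish neither condition. The upper part of the range is not small beside the target of d = 0.5. It is a consequence of the most unfavourable assumptions and should not be read as an estimate. The problem is probably smaller for children in their first year in Finnish schools than for those in regular classes.

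**What to change.** - Add one T1 item on support currently received, in or outside school, to the child, parent and teacher or welfare-body forms.
- At T2, record for each listed action the month it began and whether SB information was used to plan it.
- Enter support already running at T1 (yes/no) as a covariate in the Hypothesis 3 analyses.
- Add a sensitivity analysis restricted to children with no support running at T1, or one that compares only support begun after the T1 feedback.
- Keep ongoing support re-planned with SB output as a category of its own. Regrouping everyone by start date alone would drop it, although the protocol counts it as SB-informed.
- Do not place children with continued support in the no-support comparison.

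The cost is one extra T1 item, one or two extra T2 fields, and a smaller sample in the sensitivity analysis. The T1 item should be in place before T1, because reconstructing baseline support at the end of the year would rest on recall.
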